### Recruitment

Participants are recruited from a variety of clinical teams within mental health services across the UK. Potential participants are identified initially by clinical staff or recruited by advertisements placed in clinical settings. Those who agree are sent further information about the study and then a baseline assessment is arranged after further discussion. Assessments are conducted at the patient’s home or in clinical premises according to patient preference.

### Risk reduction

The eligibility criteria are designed to exclude people with known high risks of causing harm to themselves or other people. In addition, the gradual nature of the antipsychotic reduction will enable detection and treatment of early signs of relapse. All participants will receive usual care and monitoring of their mental state and behaviour by their clinical team. Those randomised to antipsychotic reduction will have increased contact with a psychiatrist for the duration of the reduction, mirroring usual clinical practice with someone undergoing a significant reduction of medication.

### Qualitative assessment

There will be a qualitative substudy involving around 20 to 30 participants from the antipsychotic reduction group and around 12 clinicians with experience of delivering the antipsychotic reduction programme. This study has two aims: to collect data on participant and clinician experience of trial processes, and to explore in detail experiences of antipsychotic reduction and discontinuation from the patient perspective. Participants will be identified towards the end of follow-up, using purposive sampling to obtain variation in clinical profile, experience of reduction, completion of the antipsychotic reduction protocol and experience of relapse.

Participants will be interviewed using a semi-structured interview schedule developed in collaboration with the RADAR LEAP. This will explore patients’ experiences of the intervention and its impact on their mental health and wider lives, the acceptability of antipsychotic reduction, satisfaction with available support and responses to adverse events. Interviews will be conducted with early participants following the 24 month follow-up interviews so as not to confound the main trial results. Interviews with clinicians will explore their experiences of implementing different aspects of the antipsychotic reduction strategy, relations with the research team, acceptability of medication monitoring procedures and responses to adverse events. The data will be analysed using thematic analysis.

### Statistical analysis

The primary outcome (SFS) will be analysed using generalised mixed models, accounting for baseline and treatment periods. The principal analysis will be undertaken using the intention to treat population, including all available data, without imputation. Supportive analyses will include analysis of different time periods, analysis using repeated measurements (where all subjects with data at one or more post intervention assessment will be included), exploring potential centre effects and making pessimistic assumptions by group on the patient outcome (to assess the thresholds to the impact of ‘missingness’) because of the likely pattern of data missing not at random.

The proportions of patients who experience a ‘severe relapse’ (psychiatric hospital admission) will be compared with survival analysis using Cox constant proportional hazards models and also between randomised groups at the two-year follow-up point. We will undertake supportive threshold analyses where any loss to follow-up will be considered according to extreme data patterns — for example, assuming all those who were lost in the antipsychotic withdrawal group had a relapse and all those in the maintenance group did not, and thus quantifying the extent of possible effects of missingness and thus the robustness of the main result.

A full statistical analysis plan will be completed and agreed prior to any analysis or unblinding of the data, including planned subgroup analyses and with detailed description of the statistical processes to be used.

### Economic analysis

The economic evaluation will evaluate the cost-effectiveness of the antipsychotic reduction strategy compared with maintenance treatment over 24 months. The principal analysis will be the incremental cost per quality adjusted life year gained from the health and social services cost perspective using the EQ-5D-5L to calculate quality adjusted life years (QALYs) as recommended by National Institute for Health and Care Excellence (NICE).^48^ A secondary analysis will include the cost per capability adjusted life year (CALY) gained of the antipsychotic reduction strategy compared with maintenance treatment over 24 months using the ICECAP-A, argued to have better face validity.^49^ Additional sensitivity analyses will explore the cost-effectiveness of antipsychotic reduction compared with maintenance capturing the quality of life loss associated with antipsychotics side effects using specific disutility values for antipsychotic side effects from the published literature.^50^

The WPAI questionnaire and associated formula^44^ will be used to give a monetary value to impact on employment. Health and social care data costs using published sources will be used to calculate costs for the primary health and social care analysis. A secondary analysis will be conducted from a societal perspective to capture the impact on employment, criminal justice, benefits, family and close others.

All costs and outcomes will be discounted in line with NICE guidance at 3.5% per year. Bootstrapping will be used to construct CIs for total mean costs, QALYs and CALYs and to construct cost-effectiveness acceptability curves and cost-effectiveness planes. Missing data will be handled in the same way as stated by the statistical analysis plan.

### Sample size calculation

The primary outcome is social functioning, measured using the Social Functioning Scale.^31^ The literature suggests a minimum difference of between four and five points would be clinically significant, since a difference of four to five points appears to differentiate between patients with good and poor outcomes.^37 51 52^

Using a conventional α of 5% (two-sided) and taking a SD of 8.8 derived from the literature,^53^ a sample size of 134 evaluable participants is required to provide 90% power to identify a five point difference, and a sample of 206 is required to identify a four point difference.

The trial also aimed to establish the safety of the antipsychotic reduction strategy by being powered to detect differences in rates of ‘severe’ relapse (psychiatric hospitalisation), the principal safety measure. We believe that an increased risk of up to 10% would be acceptable to many clinicians and patients if it is balanced by the important outcomes of an improvement in social functioning and reduced side effects. We derived event rates for hospitalisation from those reported in the Leucht *et al*^6^ meta-analysis of antipsychotic discontinuation studies.

We conducted a non-inferiority calculation using a 10% margin of difference. Using a non-inferiority boundary of 10% event rates (severe relapse), with an alpha of 0.05, requires a sample size of 372 for 90% power to exclude a difference of 10% between groups. Adding 15% for attrition brings this up to 402. The lower CI on the absolute scale would exclude a difference of 10% in the situation where non-inferiority was achieved. Four hundred and two participants provides 90% power to detect a difference of 3.1 points on the primary efficacy outcome (the SFS), including an allowance of 15% for attrition or unexpected challenges to the assumptions.

It is acknowledged that the non-inferiority approach may be unhelpful in these circumstances, as different people may have substantially different views on what is a reasonable non-inferiority boundary. Further, the assumptions required on issues such as the event rate for the non-inferiority assumption are strong, and modest changes in rates can have a substantial impact on the statistical power of the study making the proposed non-inferiority boundary unhelpful in certain circumstances. Thus the principal aim of the study with regards to severe relapse is to provide a robust estimate of the event rates in each randomised condition, and the difference between them, describing measurement error with appropriate CIs in order to allow individual patients and their clinicians to make an informed decision on treatment options.

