**Methods and analysis:**

This is a multicentre, randomised controlled trial involving people with schizophrenia and related disorders who have had more than one episode. Participants are randomised to have a clinically-supervised, gradual reduction of antipsychotic medication, leading to discontinuation when possible, or to continue with maintenance treatment. Blinded follow-up assessments are conducted at 6, 12 and 24 months and the primary outcome is social functioning, measured by the Social Functioning Scale at 24 months. A minimum of 134 evaluable participants provides 90% power to detect a five-point difference, and 206 to detect a four-point difference. Secondary outcomes include severe relapse (admission to hospital) and the study is also intended to detect a minimum 10% difference in severe relapse, which requires 402 participants, assuming a 15% loss to follow-up. Other secondary outcomes include all relapses, as identified by an independent and blinded endpoint committee, symptoms measured by the Positive and Negative Syndrome Scale, quality of life, adverse effects, self-rated recovery and neuropsychological measures. Enrolment started in 2016. The trial is scheduled to finish in June 2022.

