## Methods and analysis

### Study design

The trial consists of an open, parallel group randomised trial with concealed, individual randomisation. Randomisation is conducted through an independent, internet-based system linked with the database (https://www.sealedenvelope.com/randomisation/internet/) with 1:1 allocation. There are no replacements for participants who drop out or otherwise cannot comply with study procedures.

Participants and clinicians are aware of allocation, but outcome assessors are maintained blind to intervention arm as far as possible. This is achieved by nominating separate blinded and unblinded researchers at each site, and ensuring that blinded researchers are not exposed to discussions or written information that would reveal allocation. Following follow-up assessment blinded research staff record if they suspect they have guessed arm allocation.

The trial lasts for 2 years, with follow-up assessments conducted at 6, 12 and 24 months post randomisation. The trial design is presented in figure 1. Ethical approval includes the possibility of conducting a longer-term follow-up, and resources will be sought to support this at a later date.

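### The figures 372 evaluable, 15% attrition and 402 randomised in the severe-relapse sample size do not fit together

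*Protocol article*

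**What the plan says.** The section Sample size calculation in the protocol article treats severe relapse (psychiatric admission) as the principal safety measure and sizes the trial on it: "We conducted a non-inferiority calculation using a 10% margin of difference". It states that this "requires a sample size of 372 for 90% power to exclude a difference of 10% between groups", and continues: "Adding 15% for attrition brings this up to 402".

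The alpha is given as 0.05 without saying whether it is one- or two-sided for this calculation. The event rates are attributed to a cited meta-analysis of discontinuation studies, but no rate is printed.

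The same paragraph uses the total of 402 for the primary outcome: "Four hundred and two participants provides 90% power to detect a difference of 3.1 points on the primary efficacy outcome", again with a 15% allowance for attrition.

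The abstract gives the severe-relapse target as one "which requires 402 participants, assuming a 15% loss to follow-up". It does not mention 372 and attaches no power figure to relapse.

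**The concern.** The step from 372 to 402 is an increase of about 8%, although the text describes a 15% allowance. This step matters because it produces the recruitment target. The SFS calculation alone asks for only 134 to 206 evaluable participants, so severe relapse is what drives the total. If 372 is correct, the trial falls somewhat short of its stated safety power under its own attrition assumption. If 372 is not correct, the article prints a wrong requirement for its principal safety measure. Either way, a reader cannot reproduce the number on which recruitment rests.

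**Working it through.** **Inputs, all from Sample size calculation unless noted.** Required evaluable number 372 at 90% power; margin 10 percentage points; alpha 0.05, sidedness not stated; attrition 15%; total 402; SFS standard deviation (SD) 8.8, two-sided 5%, detectable difference 3.1 points. Allocation 1:1 is from Study design.

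**1. Trying to reproduce 402.**
- Standard inflation, N/(1 − d): 372/0.85 = 437.6, so 438. This is 36 above 402.
- Simple multiplication, N × (1 + d): 372 × 1.15 = 427.8, so 428. This is 26 above 402.

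Neither gives 402, and rounding cannot close gaps of this size.

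**2. What 402 does allow.**
- 402/372 = 1.081, an increase of 8.1%.
- Tolerated loss: 1 − 372/402 = 7.5%.
- Evaluable after 15% loss: 402 × 0.85 = 341.7, about 342, which is 372 − 342 = 30 short.

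**3. How the same paragraph applies 15% elsewhere.** For the SFS with 342 evaluable (171 per arm), the detectable difference at 90% power is

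8.8 × (1.960 + 1.282) × √(2/171) = 3.08 points,

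and power at 3.1 points is 0.903. The SFS sentence therefore applies a true 15% loss to 402, and it is correct as it stands.

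**4. Power for severe relapse if 372 is the true requirement.** Scaling from 372 at 90% needs no event rate:

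power = Φ[(z_α + 1.282) × √(342/372) − z_α], with √(342/372) = 0.959.

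- One-sided 0.025 (z_α = 1.960): Φ(1.148) = 0.875.
- One-sided 0.05 (z_α = 1.645): Φ(1.161) = 0.877.

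Rounding 341.7 down to 341 gives 0.874 and 0.876. The range is thus 87.4% to 87.7%, a loss of 2.3 to 2.6 percentage points.

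**5. If 372 is a slip for 342.** 342/0.85 = 402.4. Then 402, 15% and 90% agree with each other and with the SFS sentence.

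**6. Can the event rate decide between the two?** Assume, since the article does not say, equal rates p in both arms and the usual normal-approximation formula, n per arm = 2p(1 − p)(z_α + 1.282)²/0.10². The rate implied by each total is:

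| Total evaluable | One-sided 0.025 | One-sided 0.05 |
|---|---|---|
| 372 | 9.8% | 12.4% |
| 342 | 8.9% | about 11.2% |

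All four rates are of similar size and none is printed, so the article cannot settle which total was calculated. These rates are illustrative only.

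**The case against.** A reader might infer that the trial does not have its stated 90% power for severe relapse. The article does not support that as a firm conclusion. It holds only if 372 is the correct figure. The fact that 342/0.85 gives 402, and that the SFS sentence treats 402 as leaving about 342, makes a slip in 372 a real possibility. What is established is an inconsistency, not a shortfall.

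A reader might also infer that the abstract repeats the error. It does not: it gives 402 with 15% loss, without 372 and without a power figure for relapse. It is wrong only if 402 or 15% turns out to be wrong.

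The practical consequence is also limited, for three reasons:
- The closing paragraph of Sample size calculation plays down the non-inferiority test, warns that its event-rate assumptions are strong, and makes estimation with confidence intervals the principal aim for relapse.
- Outcome measures notes that admissions can be taken from patient records, so actual loss for this outcome may be below 15%.
- Statistical analysis plans a Cox model, in which participants lost early still contribute follow-up time, so counting only 342 is cautious.

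All of this stands as an argument about consequence. None of it repairs the step: the article itself applies 15% to this outcome, and no later text withdraws or corrects 372, 15%, 402 or 90%. Nor is this a detail left to the analysis plan. It is a printed calculation that fails on its own figures.

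**Conclusion.** The sample-size statement is wrong as written. That 372, 15% and 402 are inconsistent is certain and depends on no event rate and no choice of sidedness. Its effect on power is conditional. If 372 is right, power to exclude a 10-point increase at 15% loss is about 87.4% to 87.7%; this takes the stated 90% at 372 as correct and counts only participants who remain evaluable. If 342 was meant, 90% power is met and the only error is the printed 372. The article gives no means of choosing between these. The SFS power statement and the recruitment target are not called into question.

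**What to change.** Check the original calculation and keep the target of 402. Then make one of these corrections:

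- If the calculated requirement was 342, replace 372 with 342 and leave 15%, 402 and 90% as they are.
- If the calculated requirement was 372, keep it and either restate the power as about 87% with 15% attrition and 342 evaluable, or restate the tolerated attrition as 7.5% at 90% power.

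The figure of about 87% should not be adopted before that check, because it presupposes that 372 is right. In either case, print the assumed event rate and the sidedness of the 0.05 alpha that reproduce the chosen number. Change the abstract only if 402 or 15% changes.

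The cost is a text correction: no additional participants and no change to the analyses. Under the second correction, the stated power or the stated attrition allowance becomes slightly less favourable.

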## Patient and public involvement

Testing this research question is a response to a long-standing demand from the service user and carer community for an alternative to long-term antipsychotic medication. Many service users and carers are extremely concerned about the possible long-term side effects of antipsychotic medication. The study has four co-applicants with a patient or public perspective who attend project management meetings; a carer, a service user, an experienced coordinator and researcher and a staff member of a relevant charity. There is also a LEAP, made up of people with expertise in antipsychotic medication through personal use or as a carer for someone with psychosis. It meets regularly to discuss the progress of the study and to contribute to its development, for example, advising on the antipsychotic reduction strategy. The LEAP will be particularly involved in the qualitative study as part of the process evaluation. They will also be involved in providing feedback on study outputs including a regular newsletter and disseminating research results. Results of the study will be disseminated to participants at their request.

## Monitoring

The trial is monitored by a representative of the Sponsor according to the agreed trial-specific monitoring plan. A Data Safety and Monitoring Board (DSMB) and Programme Steering Committee provide independent oversight of the trial. The DSMB safeguards the interests of trial participants by assessing the safety and efficacy of the interventions during the trial, and monitoring its conduct and it makes recommendations to the steering committee. There will be no formal interim analysis, but the DSMB will continually review all adverse events data. The trial will be stopped if it is judged that there is a substantial increase in serious adverse events that are likely to be related to the intervention.

## Safety and adverse events

All adverse events are recorded with a description of the event, and are assessed for severity, causality, expectedness and seriousness.

## Ethics and dissemination

The trial was registered with the International Standard Randomised Controlled Trials register on 7 February 2017 and with ClinicalTrials.gov on 15 June 2018. All trial data is handled according to the UK Data Protection Act 1998. Substantial protocol amendments are documented and submitted for ethical and regulatory approval prior to implementation.

Written informed consent is obtained prior to participation in the trial, following a full explanation of the aims, methods, anticipated benefits and hazards of the trial. A formal assessment of each participant’s capacity to provide consent is completed first. Consent is an ongoing process and researchers ask participants for verbal consent at each follow-up time point.

Results will be published in peer-reviewed journals and disseminated to the public and the media. All contributors must meet the ‘Authorship Criteria’, as recommended by The International Committee of Medical Journal Editors.

### Current trial status

Recruitment started in March 2016 and will continue until 2020.

## Discussion

Better evidence is required about the balance of risks and benefits of a supported programme of antipsychotic reduction and discontinuation under the guidance of a clinician for the many people who have a diagnosis of schizophrenia or recurrent psychoses. The current study will be the first study conducted with people with more than one psychotic episode to employ a gradual and supported method of antipsychotic reduction, to look at a wide range of outcomes giving priority to social functioning and to follow people up for a reasonable duration. Further follow-ups are envisaged after the official end of the trial in order to provide data on longer-term outcomes.

The Dutch first-episode study suggested that long-term outcomes after a period of antipsychotic dose reduction differ from short-term outcomes.^24 54^ Although relapse rates are increased initially compared with maintenance treatment, over time these equalise. Social functioning, which was not affected in the short-term, was considerably improved by the time of the 7 year follow-up assessment. Social functioning is a measure of independence and personal efficacy. If the current trial results in improvements in social functioning this could reduce an individual’s reliance on services and produce significant economic benefits. From the individual’s point of view, better social functioning reflects a more fulfilling and socially integrated life. A strategy that can successfully reduce the use of antipsychotic medication is also likely to be associated with health benefits and improvements in quality of life secondary to the reduction of adverse effects.

The outcomes of the current trial will provide good evidence to inform patients and clinicians about the likely consequences of reducing and discontinuing long-term antipsychotic treatment in a gradual manner in a clinical setting. Many patients currently want to consider this option, but existing data on the range of relevant outcomes is limited. Providing further information will facilitate a more collaborative approach to long-term antipsychotic treatment.
